molecular-weight water-soluble dietary fibres like maltodextrin have been hypothesized to induce gastrointestinal symptoms, including osmotic diarrhea. One study reported that a 5-10 g single dose of inulin can cause abdominal flatulence in 42-50% of subjects, and diarrhoea in some cases. A number of previous studies conducted in Bangladesh and other parts of the world suggested that partially hydrolyzed guar gum (PHGG) substantially reduced the duration of diarrhea and modestly decreased stool output in acute non-cholera diarrhea in young children, indicating its potential as a new anti-diarrheal therapy for acute diarrhea in children [4, 14-16]. The evidences showed that PHGG with added oral rehydration solution enhanced early recovery of acute diarrhoea in severely malnourished children in terms of reducing the duration of diarrhoea and stool output. Similar results were also reported when PHGG was used with ORS in the treatment of acute diarrhoea in non-severely malnourished children [14].

Although diet rich in fibre is widely recommended but efficacy of fibre supplements has not been tested sufficiently in children. One study with WHO-ORS containing partially hydrolyzed guar gum (PHGG) and another PHGG supplemented comminute chicken diet have reported to reduce diarrhea duration and stool output in children with acute and persistent diarrhea, respectively. PHGG is a soluble fibre and added PHGG in the ORS or diet escapes digestion in the small intestine and enter into the colon where the fibres are expected to be fermented by colonic bacteria producing SCFAs. SCFAs will stimulate sodium and water absorption in the colon leading to early recovery from diarrhea [17].

The viscosity of resistant maltodextrin is very clear and stable and does not become cloudy or show signs of any precipitation when kept for long periods of time. It also has very good anti-acid properties and can be cooked and sterilized at high temperature in food applications due to its stability in heat processes [9].

According to a systematic review, children admitted to hospital with dehydration associated with diarrhea, reduced osmolarity rehydration solution with diarrhea is associated with reduced need for unscheduled intravenous infusions, lower stool volume, and less vomiting compared with standard WHO rehydration solution. Children with acute diarrhea, therefore, may benefit from a reduced osmolarity ORS solution [18-21].

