Dietary fibres can act by changing the nature of the contents of the gastrointestinal tract and by changing how other nutrients and chemicals are absorbed [22]. Advantages of consuming fibre are the production of healthful compounds during fermentation, increased bulk of stool, softening of stool, shortening of transit time through the intestinal tract, blocking of intestinal mucosal adherence, translocation of potentially pathogenic bacteria, and modulation of intestinal inflammation [23-27]. Based on literature review we are hypothesizing that resistant maltodextrin, a water-soluble, nonviscous and highly digestion-resistant maltodextrin is digestively tolerable and may not cause gastrointestinal symptoms including diarrhea in young healthy children. Additionally, it is hypothesized that resistant maltodextrin with ORS will be efficacious in the treatment of watery diarrhea in young children.

The objectives of the present study are to assess the digestive tolerability of the resistant maltodextrin in children which includes abdominal pain, rumbling, bloating, flatulence, and stool consistency. Additionally, the study will examine whether resistant maltodextrin and ORS can reduce duration of watery diarrhea and stool output in children 1-3 years.

It is a water-soluble dietary fiber (digestion resistant dextrin) which can easily be taken every day. It easily gets dissolved in water without changing its smell and taste at all. It can also be dissolved in any drink that one likes. Resistant maltodextrin contains 90% dietary fiber (dry solid base) which helps reduce absorption of sugar and fat so that the rise of blood sugar level and blood RLP-

cholesterol level after meal would be low. Adults are advised to have one packet (as dietary fiber 5g) per meal. Three packets per day are standard. It is advised to dissolve the packet in any drink and have that with meal.

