### *Study design of exploratory study*

We will conduct the study in two phases – in phase I the safety and tolerability issues will be examined among healthy **and diarrheal** children ( $n=30+30=60$ ), and if Fibersol-2 is found to be safe and tolerable, we will approach the DSMB to seek permission to extend the study for phase II as the clinical trial only in diarrheal children. The evaluable clinical signs include abdominal pain, rumbling, bloating, flatulence, and stool consistency.

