## Definitions

**Abdominal distension** occurs when substances, such as air (gas) or fluid, accumulate in the abdomen causing its outward expansion beyond the normal girth of the stomach and waist. It will be evaluated by regular measurement of abdominal girth. No set parameters for abdominal distension. To measure the abdominal girth before the IP and repeat measurement daily. If there is change that is increase in diameter of girth measurement, then we will define distension. Recurrent abdominal pain or discomfort at least 3 days/month in the last 3 months. [28, 29]

**Abdominal pain:** Abdominal pain is felt in the part of the trunk below the ribs and above the pelvis. Abdominal pain comes from organs within the abdomen or organs adjacent to the abdomen. It will be measured by asking mother's perception whether the child had the history of cry, irritability which was associated with abdominal pain. [28]

**Rumbling:** A stomach rumble, also known as a bowel sound or peristaltic sound, is a rumbling, growling or gurgling noise produced by movement of the contents of the gastro-intestinal tract as they are propelled through the small intestine by a series of muscle contractions called peristalsis. It will be measured both by taking history from the parents and by abdominal auscultation.

**Bloating:** Bloating is the presence of abnormal general swelling, or increased in diameter of the abdominal area. Recurrent feeling of bloating or visible distension at least 3 days/month in the last 3 months [28]. It will also be evaluated by regular measurement of abdominal girth.

Flatulence: "flatus expelled through the anus" or the "quality or state of being flatulent", which is defined in turn as "marked by or affected with gases generated in the intestine or stomach; likely to cause digestive flatulence". It will be measured by taking history from the parents.

Stool consistency: Appearance of the stool; such as formed, mucoid, or liquid. This will be measured by direct visualization by the parents as well treating physicians.

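### The flatulence definition has no threshold, grade or comparison with the child's usual state, so this phase I tolerability sign separates product effect from normal wind, and one dose from the other, poorly

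*Protocol*

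**What the plan says.** **Role of the sign.** The Protocol, under Study design of exploratory study, states: "The evaluable clinical signs include abdominal pain, rumbling, bloating, flatulence, and stool consistency". The same section makes phase I the basis for asking the DSMB to allow phase II. The end of the background section says that phase I compares two doses and that the more suitable one goes into the clinical trial.

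**Definition.** Under Definitions, flatulence is given two alternatives joined by *or*. The first is "flatus expelled through the anus". The second is the quality or state of being flatulent, explained in turn as "marked by or affected with gases generated in the intestine or stomach; likely to cause digestive flatulence". The only statement on ascertainment is: "It will be measured by taking history from the parents".

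**Groups.** Methods for exploratory study sets 15 children per dose among healthy children and 15 per dose among diarrheal children. All four groups receive Fibersol-2.

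**Background.** The Introduction mentions flatulence after another fibre: "One study reported that a 5-10 g single dose of inulin can cause abdominal flatulence in 42-50% of subjects". It also says that "water-soluble dietary fibres like maltodextrin have been hypothesized to induce gastrointestinal symptoms, including osmotic diarrhea". For resistant maltodextrin itself, the stated hypothesis is that it "is digestively tolerable and may not cause gastrointestinal symptoms including diarrhea in young healthy children".

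**The concern.** The text is a dictionary entry used as a case definition. Passing some wind is a normal event, and because the two alternatives are joined by *or*, the first is enough on its own. The second refers to a flatulent state, but it is circular, has no threshold, and cannot narrow a definition that the first already satisfies.

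The same section treats abdominal distension differently: girth is measured before the product and repeated daily, and an increase defines the sign. Flatulence has no such reference within the child. Nor is there one between groups, since nobody in phase I is untreated or on placebo.

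At stake is whether one of the five signs can inform the tolerability judgement and the dose choice. If ordinary wind is counted, the rate at each dose is a mixture of product effect and background, and the difference between doses shrinks. If it is not counted, the result depends on each parent's own idea of what is worth mentioning, which the plan does not standardise.

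**Working it through.** The Protocol gives no expected rate, power or sample size for flatulence, so there is no figure of the plan's own to reproduce. What follows illustrates how fast the contrast between doses is lost.

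**Inputs**
- Group size: 15 per dose in each cohort (Methods for exploratory study). Pooling the two cohorts would give 30 per dose; the Protocol does not plan this.
- Test and level: chi-square for categorical variables, two-sided 5% (Statistical methods).
- True rate of excess flatulence at the higher dose: 50%. This is an assumption, borrowed from the upper end of the inulin range in the Introduction.
- True rate at the lower dose: 20%. This is an assumption. A second case uses 10%.
- *f*, the share of unaffected children who are nevertheless counted as positive: not given in the document, so it is varied from 0 to 0.9.

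**Formulas**
- Observed rate: *q* = *p* + (1 − *p*) × *f*.
- Observed difference between doses: (1 − *f*) × (*p*_high − *p*_low).
- Power: the sum of the binomial probabilities of all pairs of counts for which the uncorrected Pearson chi-square reaches the 5% level.

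Example at *f* = 0.5: lower dose 0.20 + 0.80 × 0.5 = 0.60; higher dose 0.50 + 0.50 × 0.5 = 0.75. The true difference of 30 points becomes 15.

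**Results, true rates 20% v 50%**

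| *f* | Observed rates | Difference | Power 15 v 15 | Power 30 v 30 (if pooled) |
|---|---|---|---|---|
| 0 | 20% v 50% | 30 points | 0.42 | 0.69 |
| 0.1 | 28% v 55% | 27 points | 0.32 | 0.57 |
| 0.2 | 36% v 60% | 24 points | 0.25 | 0.47 |
| 0.5 | 60% v 75% | 15 points | 0.15 | 0.23 |
| 0.9 | 92% v 95% | 3 points | 0.015 | 0.06 |

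**Second case, true rates 10% v 50%.** Power at 15 v 15 is 0.73 at *f* = 0, 0.21 at *f* = 0.5 (observed 55% v 75%) and 0.02 at *f* = 0.9 (observed 91% v 95%). At 30 v 30 it is 0.95, 0.36 and 0.08.

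**Choice of test.** Fisher's exact test gives lower values and the same pattern. For 20% v 50% at 15 v 15, power is 0.25 at *f* = 0, 0.06 at *f* = 0.5 and 0.003 at *f* = 0.9.

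The attenuation factor (1 − *f*) applies to the descriptive difference whether or not a test is done. Near-universal positivity is not needed for a serious loss: at *f* = 0.5 half of the difference has gone.

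**The case against.** **The positive rate is not known.** A reader might infer that nearly every child would be positive, that the sign would show nothing, or that an excess at the higher dose could not appear. The document does not support that. Ascertainment is by parental history, and parents may report only wind they find noticeable. At *f* of 0.1 to 0.2 a good part of the contrast survives. This objection stands, and the conclusion is limited accordingly. What remains is that the result then rests on an unstated threshold that varies by parent.

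**The background does not predict flatulence for this product.** A reader might take the Introduction to say that flatulence is the expected effect of Fibersol-2, or the sign most likely to respond to dose. It says neither. The figure of 42-50% is for a single dose of inulin, no dose-response is reported, and the Protocol's own hypothesis is that resistant maltodextrin may not cause symptoms. This also stands. The 50% above is only a borrowed value. Testing a hypothesis of no symptoms still needs a measure that could contradict it.

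**Phase I is exploratory and not powered for a dose contrast.** This is true: the review committees suggested its size, and even a clean measure gives only 0.42 at 15 v 15 in the main case. The power figures serve to show relative loss. The mixing of background with product effect is the same in a purely descriptive table.

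**One sign decides nothing alone, and a questionnaire may hold the detail.** No rule makes flatulence decisive, so it cannot be said that the product would fail on it or that the sign would be ignored. The Protocol mentions a field-tested questionnaire that is not shown, and it may contain a grade or recall period. But the definition is stated in the Protocol, and a form that followed it faithfully would inherit the fault. This is a badly stated rule and not detail left for later.

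**Conclusion.** The concern holds as a defect of definition. The first alternative, taken as written, counts normal passing of wind. Nothing in the definition sets a threshold, a grade or a comparison with the child's usual state, and no untreated phase I group supplies the background rate. The sign therefore discriminates poorly between product effect and normal wind, and between the two doses.

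The size of the loss cannot be fixed from the document. Under the assumed 20% v 50%, power at 15 v 15 falls from 0.42 to between 0.32 and 0.015 as the share of unaffected children counted rises from 10% to 90%. If the cohorts were pooled, it falls from 0.69 to between 0.57 and 0.06. Those values rest on the assumed true rates and on the same share being miscounted at both doses.

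The consequence is limited to one of five signs, but that sign informs the dose choice and the request to proceed to phase II. The definition should be corrected.

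**What to change.** Replace the dictionary text under Definitions with an operational rule:

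- Each day, ask the parent about the child's passing of wind in the last 24 hours, with three answers: none, usual for this child, more than usual for this child.
- Record the reference level before the first dose, and count only *more than usual* as positive.
- Use the same question, asked in the same way, for both doses.
- In healthy children, take the reference from the 7-day pre-study observation. The Protocol describes that period only for control group children, so it cannot be assumed to exist for the hospital cohort.
- In diarrheal children, take the reference just before the first dose, during the illness, and report this cohort separately, because illness also affects gas.

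**Cost.** One extra line on the form and a replaced sentence in the Protocol. No visits are added: staff already give the product twice daily and collect 1-day recall data in the week after. The limitation is residual confounding in the diarrheal cohort, where a change from the pre-dose level may reflect the course of the illness as well as the product.

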### **Sample Size Calculation and Outcome (Primary and Secondary) Variable(s)**

Clearly mention your assumptions. List the power and precision desired. Describe the optimal conditions to attain the sample size. Justify the sample size that is deemed sufficient to achieve the specific aims.

Based on the results of a clinical trial of ORS solution in children with acute watery diarrhea with an anticipation of a 25% reduction in 48-hour stool output after in children after receiving Fibersol-2 dissolved with drinking water. Considering 5% level of significance and 90% power and 10% drop out the sample size is estimated to be 46 in each group [14]. However, for the tolerability and acceptability study we have selected 30+30=60 children suggested by the respected members of the RRC and ERC respectively.

For the tolerability and acceptability study in healthy Study group 1, 15 healthy children will receive Fibersol-2, 2.5 mg twice daily

Study group 2, 15 healthy children will receive Fibersol-2, 5mg twice daily

For the tolerability and acceptability study in children with diarrhea Study group 1, 15 diarrheal children will receive Fibersol-2, 2.5g twice daily

Study group 2, 15 diarrheal children will receive Fibersol-2, 5g twice daily

For RCT in diarrheal children:

Study group 1, 46 will receive Fibersol-2 dissolved in 50 ml drinking water, twice daily (suitable dose from the tolerability and acceptability trial)

Study group 2, 46 will placebo (regular maltodextrin) dissolved in 50 ml drinking water, twice daily (same dose as in Fibersol-2)

### **Data Analysis**

Describe plans for data analysis, including stratification by sex, gender and diversity. Indicate whether data will be analysed by the investigators themselves or by other professionals. Specify what statistical software packages will be used and if the study is blinded, when the code will be opened. For clinical trials, indicate if interim data analysis will be required to determine further course of the study.

### **Statistical methods**

All data will be entered into microcomputer and analyzed using the software 'Statistical Package for Social Science'; version 20.0, Chicago, IL. Continuous variables will be compared between groups with student's t-test and nonparametric test. Categorical variables will be compared by chi-square test. Kaplan-Meier survival curves will be constructed for the duration of diarrhoea and for comparison with log rank test; a p value <0.05 will be considered as statistically significant. To see

whether there are significant differences among the groups, we will perform ANOVA to systematically examine variability within groups being compared.

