#### **Baseline information**

Children fulfilling the eligibility criteria will stay in the hospital throughout the study period until discharged. Research physician will take a detailed medical history of the enrolled children to determine the duration of and type of diarrhoea and its frequency; duration and frequency of vomiting; and presence of other symptoms such as fever, feeding difficulties, and treatment received for the illness before admission; and perform a thorough physical examination including assessment of dehydration according to the guidelines used in icddr,b and also the nutritional status will be measured and recorded.

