### Output (stool, urine and vomitus)

Stool will be collected in a bucket of known weight beneath the cholera cot with a central hole and will be measured every 6 hours with an electronic scale of a precision of 1 gram. Urine will be collected by pediatric urine collector (PUC bag) and measured with a calibrated cylinder in ml. Vomitus will be collected in a pre-weighed bowl and measured with an electronic scale. The children will be offered a defined food of known calorie after measuring with an electronic scale of precision 1 g. Any leftover will be measured and subtracted from the amount offered and amount ingested will be recorded every 6 hours. Nude body weight will be measured at admission, after rehydration, and every 6 hours until recovery from diarrhoea and then at the end of every 24 hours and at discharge. Clinical evaluation will be performed every morning and evening. Resolution of diarrhea will be defined as the passage of two consecutive soft/formed stools or no stool for 24 hours. Therapeutic success will be defined as the cessation of diarrhea within 7 days of inclusion in the study treatment. Duration of diarrhea will be calculated in hours from the time of randomization to the last watery or loose stool within 7 days. Children will be considered withdrawn from the study if their parents or legal guardian withdraw consent, or the child is withdrawn from study for treatment of any complications; data (intakes and outputs) of such children up to the time of withdrawal will be included in the analysis (intent to treat analysis). Data of the children who failed to recover within seven days (study period) will also be included in the analysis for a maximum of seven days; those will be labelled as therapeutic failures and will be treated in the hospital until recovery.

Primary outcome measures will be; duration of diarrhea, proportion of patients recovered within 72 hours, and daily stool output.

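### Stool output is to be compared by an unadjusted t-test and an unnamed nonparametric test with no rule for which decides; one pre-specified covariate-adjusted model would use baseline data already collected

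*Protocol*

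**What the plan says.** The Statistical methods section of the Protocol gives one sentence for all continuous outcomes: "Continuous variables will be compared between groups with student's t-test and nonparametric test". The nonparametric test is not named, and no rule says which result decides. The section then adds that, to see "whether there are significant differences among the groups, we will perform ANOVA to systematically examine variability within groups being compared". No covariate, transformation or adjusted model appears.

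This sentence governs stool output. The section on output measurements lists it as primary: "Primary outcome measures will be; duration of diarrhea, proportion of patients recovered within 72 hours, and daily stool output". The sample size section rests on "an anticipation of a 25% reduction in 48-hour stool output" and continues: "Considering 5% level of significance and 90% power and 10% drop out the sample size is estimated to be 46 in each group".

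Baseline data are collected regardless. Under Baseline information the research physician takes a history to "determine the duration of and type of diarrhoea and its frequency" and assesses dehydration. Under Output, "Nude body weight will be measured at admission, after rehydration, and every 6 hours until recovery from diarrhoea". Stool is weighed to 1 gram, and no scaling to body weight is stated.

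**The concern.** Children of 1–3 years differ in size, and they enter with up to 7 days of illness, so part of the spread in stool output is plausibly predictable from what is known at entry. An unadjusted comparison leaves that part in the error term. The trial is small: 46 per arm, about 41 after the planned 10% dropout. The Protocol gives no standard deviation to show that there is power to spare.

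Separately, joining two tests with no order between them means that a result could be claimed if either falls below 0.05. At stake are some precision and a small excess of false positives. The validity of the randomized comparison is not in question.

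**Working it through.** **1. The plan's own figure.** Work in units of the control mean, so that the difference is 0.25 and the standard deviation is the coefficient of variation (CV). For two-sided 5% (sidedness is not stated, so this is assumed) and 90% power:

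n per arm = 2 × (1.960 + 1.2816)² × (CV/0.25)² = 21.015 × (CV/0.25)²

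The Protocol gives neither mean nor standard deviation, so 46 cannot be reproduced, only solved backwards. With CV = 0.349: 21.015 × 1.949 = 40.95, so 41, and 41/0.9 = 45.6, so 46. The range of CV that returns 46 is 0.345–0.349. It is 0.366–0.369 if dropout was not added, and 0.383–0.386 if the test is one-sided with dropout added.

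**2. Unadjusted power at 41 per arm.** d = 0.25/0.3492 = 0.716. Noncentrality = 0.716 × √(41/2) = 3.24 on 80 degrees of freedom. Power is 89.3% (90.0% by the normal approximation).

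**3. Adjusted power.** Let R² be the share of within-arm variance that the covariates explain. It is an assumption. Charge k = 4 covariates for degrees of freedom and chance imbalance:

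noncentrality = d × √(41/2) × √(1 − k/80) / √(1 − R²), on 80 − k degrees of freedom

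| R² | 1/(1 − R²) | Power, CV 0.349 | Power, CV 0.5 | Power, CV 0.8 |
|---|---|---|---|---|
| unadjusted | – | 89.3% | 60.9% | 28.7% |
| 0 | 1.00 | 87.7% | 58.7% | 27.5% |
| 0.05 | 1.05 | 89.3% | 60.8% | 28.7% |
| 0.10 | 1.11 | 90.8% | 63.2% | 30.0% |
| 0.20 | 1.25 | 93.7% | 68.3% | 33.1% |
| 0.30 | 1.43 | 96.1% | 74.0% | 37.0% |

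Break-even is where (1 − 4/80)/(1 − R²) = 1, that is R² = 0.05. With three covariates it is 3/80 = 0.0375. The second column is the equivalent gain in children, 11–43% for R² of 0.1–0.3, before the charge. Confidence intervals narrow by the factor √(1 − R²), which is 0.95 to 0.84 over that range.

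**4. Two tests, either may count.** With no true effect, 41 per arm, lognormal output with CV 0.6 (assumed) and 20,000 simulated trials, the t-test and the rank test each reject in about 4.9%. At least one rejects in 6.7–6.9% across repeat runs. The simulation standard error is √(0.067 × 0.933/20,000), about 0.18 points, and the figure moves a little with the assumed distribution.

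**5. ANOVA.** With two arms F = t², so the p-value is the t-test's. It adds neither information nor a further chance of a false positive.

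**6. Scale.** The planned effect is a ratio, while the t-test compares raw means. In a lognormal model with ratio 0.75 and 41 per arm, raw versus log-scale power is about 96% v 97% at CV 0.35, 90% v 92% at 0.40 and 58% v 64% at 0.6. Near the implied CV the log scale adds only 1–2 points. These figures are not comparable with the table, because in this model the standard deviation falls with the mean.

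**The case against.** The strongest reply is that covariates, transformation and sensitivity analyses are commonly left to a statistical analysis plan, which is not shown, and that the sentence on continuous variables is generic. That limits the point but does not remove it. The Protocol does not defer the choice: it states a method, and it joins two tests without saying which decides.

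It is also fair that the gain is assumed. No R-squared, mean or standard deviation is given. Children are randomized immediately after admission, so no pre-randomization stool weight is planned, and history items may be only weakly prognostic. That stands.

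Four stronger readings are tempting, and the documents do not support them.

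- A reader might infer that the unadjusted test is wrong or biased. Under randomization it is valid.
- A reader might infer a large power deficit by taking a CV of 0.6 or 0.8. The Protocol gives no CV. The figure implied by 46 per arm is about 0.35, where the gain is modest. Whether that variance is realistic is a separate question about the sample size.
- A reader might count three tests. ANOVA duplicates the t-test in two arms, and the Protocol also has four phase 1 groups, for which it may be meant.
- A reader might take it as settled that output is skewed and will be analysed in raw grams. The Protocol says how stool is weighed, not the unit of analysis, and says nothing about its distribution.

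**Conclusion.** The point holds as a cheap improvement. The stated analysis is valid but leaves recorded baseline information unused and does not say which of two tests decides.

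At the implied CV of about 0.35, with four covariates charged, power goes from about 89% to 91–96% if R-squared is 0.1–0.3. It goes slightly down if R-squared is below about 0.05. Gains are larger only if the true CV is higher: at an assumed CV of 0.5, from 61% to 63–74%. The excess type I error from an either-test rule is under 2 percentage points. All of this rests on an assumed R-squared, two-sided 5% testing and 41 evaluable children per arm.

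**What to change.** For the randomized trial, replace the sentence as it applies to stool output with one primary analysis: a linear model for stool output per kg admission weight, with arm and a few pre-specified baseline covariates. These would be pre-admission diarrhoea duration and stool frequency, plus dehydration grade if both grades are enrolled. On that last item the inclusion criteria allow none or some dehydration, while the opening paragraph of the methods for the efficacy trial names only no dehydration. The two passages must be reconciled first.

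In addition:

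- State whether the outcome is 48-hour output, as in the sample size section, or daily output, as in the list of primary outcomes.
- If a ratio is wanted to match the planned 25% reduction, use a log link, or a log scale with a stated rule for zero output. Zeros are to be expected on single days, because a day without stool is one of the definitions of resolution.
- Name the rank test and keep it as a sensitivity analysis only.
- Do not use ANOVA as a further test of the two trial arms.
- For duration of diarrhoea, add a Cox model with the same covariates. A log-rank test stratified on several factors would be too sparse in 92 children.

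The cost is a few lines of text and no new data. The downside is a few degrees of freedom and, if a ratio is used, a changed effect scale.
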